**Anticipated results:**

We hypothesize that Group 3 (combined stimulation) will yield the greatest reduction in spasticity (MAS decrease ≥ 1) and the most significant improvements in upper-limb function (FMA-UE, ARAT) compared to Groups 1 and 2. These clinical gains are expected to correlate with neurophysiological changes (MEP amplitude, cortical silent period), supporting the central-peripheral synergy model.

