## Methods

### Study design

The study is a prospective, single-center, randomized, parallel-controlled design. Fifty-four patients will be randomly assigned to one of three groups (Figure 1): (1) active iTBS+sham cTBS; (2) sham iTBS+active cTBS; (3) active iTBS+active cTBS in 1:1:1 ratio. The trial comprises three phases (Table 1): baseline assessment, post-training assessment (i.e., after 10 sessions) and follow-up assessment (i.e., 2 weeks after the completion of all training sessions). Intervention will be conducted five sessions a week, with a total of 10 sessions. All participants will sign an informed consent form. Adverse reactions will be handled in accordance with the preset protocol. The whole study will be performed at the Department of Rehabilitation Medicine of South China Hospital of Shenzhen University (Shenzhen, Guangdong Province, China). The results will be published in peer-reviewed journals and reported at academic conferences. The protocol is registered with Chinese Clinical Trial Registry (Registration No. ChiCTR2500105190). The trial will be conducted in accordance with the Consolidated Standards of Reporting Trials (CONSORT) guidelines, and the study protocol has been approved by the Institutional Review Board of Ethics Committee of South China Hospital of Shenzhen University (grant no. HNL.S2025041).

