### CPT

After receiving iTBS, cTBS or sham stimulation to the spastic muscle or the antagonist, all participants will undergo a 30-min session of CPT delivered by licensed therapists. Each session will consist of physical modalities, occupational therapy task training, and manual massage/manipulation. The therapy will be provided Monday through Friday throughout the 2-week intervention period.

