### Statistical analysis

For this study, MEP data will be processed and analyzed statistically using the Statistical Package for the Social Sciences (SPSS, version 26.0). For normally distributed continuous data, repeated-measures analysis of variance will be used for intra-group comparisons and independent-samples *t*-test for inter-group comparisons; for non-normal data, Friedman test and Wilcoxon rank-sum test will be adopted; for count data, Pearson χ^2^ test will be employed. The intraclass correlation coefficient (ICC) will be used to assess the inter-rater reliability of MEPs and MAS (17), and Cronbach's α coefficient will be used to test the internal consistency of scales. A *p* value < 0.05 will be considered statistically significant. The measurement of MEPs will follow the guidelines of the International Federation of Clinical Neurophysiology (27), and the FMA-UE will refer to the criteria for clinically important differences (22). To investigate the therapeutic mechanism, we will examine the association between changes in neurophysiological measures and improvements in clinical behavioral outcomes. Specifically, we will calculate the change scores (from baseline to post-intervention) for each participant in MEP amplitude (or cortical silent period) and in the Fugl-Meyer Assessment for Upper Extremity (FMA-UE) scores. We will then use Spearman correlation analysis to determine whether a significant correlation exists between these two change scores. We hypothesize that participants with greater clinical improvement will also exhibit more pronounced beneficial changes in corticospinal excitability.

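### The therapeutic-mechanism analysis correlates two change scores with no treatment term stated, so a significant result shows association between participants, not a mechanism of stimulation

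*Protocol article*

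**What the plan says.** The Introduction of the protocol article lists neurophysiological mechanisms among the primary objectives. The Statistical analysis section sets the aim: "To investigate the therapeutic mechanism, we will examine the association between changes in neurophysiological measures and improvements in clinical behavioral outcomes". The variables are changes from baseline to post-intervention in MEP amplitude, or alternatively cortical silent period, and in FMA-UE. The test follows: "We will then use Spearman correlation analysis to determine whether a significant correlation exists between these two change scores". The section's general threshold applies: "A *p* value < 0.05 will be considered statistically significant". The attached hypothesis is that "participants with greater clinical improvement will also exhibit more pronounced beneficial changes in corticospinal excitability". The section does not say whether the correlation is pooled over arms, computed within arm or adjusted for anything.

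The Abstract (Anticipated results) first hypothesises that Group 3 will improve most on spasticity and function, and then adds: "These clinical gains are expected to correlate with neurophysiological changes (MEP amplitude, cortical silent period), supporting the central-peripheral synergy model".

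Three other features matter. Under Study design, each arm has at least one active stimulation and none is sham plus sham. Under CPT, "all participants will undergo a 30-min session of CPT delivered by licensed therapists". Under the inclusion criteria, patients are 3–12 months after stroke.

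The Statistical analysis section also plans between-group comparisons by t-test or rank-sum test, and names MEP data as part of what is analysed. It does not connect those comparisons to the mechanism question.

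**The concern.** The question is causal: does stimulation improve function by changing corticospinal excitability? The test asks something else: do participants who change more on MEP also change more on FMA-UE? Randomised arm, the only feature of the trial that separates treatment from everything else, is not a stated input.

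Time since stroke, corticospinal integrity and response to conventional therapy could each make some patients gain more on both measures. Any of them gives a positive correlation with no contribution from stimulation. A significant result would then be reported as insight into the therapeutic mechanism, which is a primary objective, and cited in support of the synergy model. Synergy is a statement about Group 3 against Groups 1 and 2, and a correlation without arm does not address it.

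**Working it through.** The article gives no expected correlation, power or sample size for this test, so there is no figure of its own to reproduce.

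**Inputs.** From Sample size estimation: 54 recruited (18 per arm), at least 45 completers (15 per arm). From Statistical analysis: Spearman test, p < 0.05. Assumption, not in the article: the correlation r between the two changes that arises from shared recovery alone, taken over 0.1 to 0.5.

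**Step 1: approximate check by formula.** For bivariate normal changes with correlation r, the Spearman correlation is ρs = (6/π)·arcsin(r/2). With z = atanh(ρs) and SE = √(1.06/(N−3)), the chance of significance is Φ(z/SE − 1.96) + Φ(−z/SE − 1.96). At N = 45, SE = √(1.06/42) = 0.159.
- r = 0.1: ρs = 0.096, z = 0.096, z/SE = 0.60, chance 9%.
- r = 0.3: ρs = 0.288, z = 0.296, z/SE = 1.86, chance 46%.
- r = 0.5: ρs = 0.483, z = 0.526, z/SE = 3.31, chance 91%.

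**Step 2: simulation.** Three equal arms, bivariate normal change scores with SD 1, no stimulation effect in any arm, 20,000 replicates. The last column requires both an overall arm effect on MEP change and the arm-adjusted association. Percentage of trials significant, N = 45 / N = 54:

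| r | Spearman, no arm term | Rank correlation adjusted for arm | Arm effect on MEP and adjusted association |
|---|---|---|---|
| 0.1 | 10 / 10 | 10 / 10 | not run |
| 0.2 | 24 / 28 | 23 / 27 | 1.0 / 1.2 |
| 0.3 | 48 / 56 | 46 / 54 | 2.0 / 2.6 |
| 0.4 | 74 / 82 | 72 / 80 | 3.2 / 3.7 |
| 0.5 | 92 / 96 | 91 / 96 | 4.1 / 4.7 |

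Repeat runs differ by a point or so (92% to 93% at r = 0.5, N = 45). The test of arm on MEP change stays at 5% throughout.

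**Step 3: reading.** The second column falls short of a cure because arm does not explain shared recovery: the association sits within arms. Only a comparison between randomised arms holds its 5% rate when stimulation does nothing.

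**Step 4: what a between-arm contrast cannot do.** If every participant in every arm gains 0.8 SD on both measures, with r = 0, the Spearman test is significant in about 5% of trials. The contrast of Group 3 with Groups 1 and 2 combined on MEP change is also significant in about 5%. Neither sees a shift common to all arms.

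**Step 5: a shift in Group 3 only.** If only Group 3 gains 0.8 SD on both measures (N = 45), the Spearman test is significant in about 12% to 13% of trials when r = 0, but in about 72% to 73% when r = 0.3. The Group 3 versus Groups 1 and 2 contrast on MEP change is significant in about 70% either way. The correlation's behaviour is governed largely by the assumed r, while the contrast's is governed by the arm effect.

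**The case against.** Several points on the other side are sound.

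- **Type I error.** A reader might take 48% against a nominal 5% as an inflated error rate. It is not. The association in those simulations is real, and the test fits the hypothesis the section attaches to it. The fault lies in the label and the inference.
- **A missed uniform mechanism.** A reader might infer that Spearman is at fault for missing a mechanism that shifts all patients alike, and that a between-arm contrast would recover it. Step 4 shows that it would not. The limit comes from having no sham-plus-sham arm. Nor is the low detection rate for a Group 3-only shift general: it rises from about 12% to about 73% once r is 0.3.
- **Between-group MEP comparisons.** These are already planned, so it would be wrong to say that the trial lacks a randomised look at MEP. What is missing is the link from them to the mechanism claim, and the baseline adjustment.
- **The Abstract.** It does not rest synergy on the correlation alone, because the preceding sentence expects a Group 3 advantage. With no stimulation effect, requiring both a Group 3 contrast on FMA-UE and the correlation gives only about 2% to 3% at r = 0.3. Still, the sentence gives the correlation a supporting role that it cannot carry.
- **Silence on arm.** The article is condensed and an analysis plan may stratify or adjust by arm. That would not remove the problem (Step 2, second column).
- **A null result.** Nothing in the article says that one would be read as evidence against a mechanism, so that is not claimed here.

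**Conclusion.** The point holds in this form: the article fixes, for a primary objective, a test whose null hypothesis is not the absence of a treatment mechanism. With no stimulation effect and 45 completers, it is significant in about 10% of trials at a shared-recovery correlation of 0.1, about half at 0.3 and about 93% at 0.5. That range rests wholly on an assumed correlation, since the article gives none, and on normal change scores with equal arms. A significant result would be a true association between participants, but neither evidence of therapeutic mechanism nor, by itself, support for synergy. The documents do not support the stronger readings that the test's error rate is invalid or that a different analysis would detect an effect common to all arms.

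**What to change.** In the Statistical analysis section:

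1. Base the mechanism claim on the between-arm MEP comparisons already planned. Specify them as Group 3 versus Group 1 and Group 3 versus Group 2 at post-intervention, adjusted for baseline MEP, and read them together with the same baseline-adjusted contrasts on FMA-UE.
2. Report the change-score correlation as descriptive, within arm, with a 95% confidence interval.
3. State that, without a sham-plus-sham arm, conclusions are limited to differences between the three regimens. An effect common to all arms cannot be attributed to stimulation by the correlation or by these contrasts. A positive contrast on both measures does not prove mediation.

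In the Abstract (Anticipated results), reword the sentence so that a correlation is not itself said to support the synergy model.

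The cost is revised wording and a few baseline-adjusted models on data already to be collected. The price is a more modest mechanism claim. The separate pairwise contrasts also have less power than a pooled one: about 56% to 57% against 70% at 0.8 SD with 15 per arm, before any gain from baseline adjustment.

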### Sample size estimation

As the differential effects of priming iTBS on hemiparetic upper-limb training have yet to be examined, we based our sample-size estimate on existing three-group trials. A recent meta-analysis reported a pooled Cohen's *d* = 0.60 favoring iTBS for upper-limb motor improvement. For a three-group design, this translates to an effect size *f* of ~0.30 (15). *A priori* power analysis (power = 0.80, two-tailed α = 0.05) indicated that 45 participants would be required. Accounting for an anticipated 15% dropout rate, we will recruit 18 participants per group, for a total sample size of 54. This recruitment target is expected to yield at least 45 participants completing the trial.

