### Outcome measures

MEPs are compound muscle action potentials recorded from a target muscle after a single-pulse TMS over the primary motor cortex; they provide an objective index of corticospinal excitability and conduction integrity, with excellent test-retest reliability [Intraclass Correlation Coefficient (ICC) = 0.75–0.94, Kendall's tau = 0.81] (17). In this trial, MEPs will be used to quantify corticospinal plasticity before and after the intervention.

Although the pTBS intervention targets the forearm muscles (FCR and ECRL), MEPs were recorded from the abductor pollicis brevis (APB) because it is a standard target muscle in TMS studies, recommended for its consistent and robust MEP responses and well-defined cortical representation in the primary motor cortex (M1) hand area (17). This approach provides a reliable and comparable measure of overall corticospinal excitability.

Briefly, Ag/AgCl surface electrodes will be placed over the abductor pollicis brevis of the paretic limb. A Magstim 200^2^ stimulator with a 70-mm figure-of-eight coil will deliver 0.2-Hz stimuli to the affected-hemisphere M1 hand area while the participant rests. The following metrics will be obtained: (1) resting motor threshold (RMT), defined as the lowest stimulus intensity eliciting ≥ 50 μV MEPs in ≥ 5 of 10 consecutive trials (17); (2) MEP peak-to-peak amplitude (mV) measured at 120%RMT, averaged across 10 artifact-free trials, as a marker of corticospinal excitability; and (3) MEP latency (ms) from stimulus artifact to onset of the first deflection, reflecting central conduction time. All measurements will be performed by the same assessor at baseline, immediately post-intervention, and at the 2-week follow-up to ensure consistency.

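### The mechanism correlation uses MEP change on the millivolt scale, which can carry baseline corticospinal integrity into the link with FMA-UE gain; Spearman ranking does not remove this.

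*Protocol article*

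**What the plan says.** Outcome measures defines the amplitude metric as "MEP peak-to-peak amplitude (mV) measured at 120%RMT, averaged across 10 artifact-free trials". Statistical analysis then states, for the mechanism question, that "we will calculate the change scores (from baseline to post-intervention) for each participant in MEP amplitude" and in FMA-UE, and continues: "We will then use Spearman correlation analysis to determine whether a significant correlation exists between these two change scores". The stated hypothesis is that patients who improve more clinically also show larger beneficial changes in corticospinal excitability.

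For arm comparisons the same section gives the independent-samples t-test for normal data, and "for non-normal data, Friedman test and Wilcoxon rank-sum test will be adopted". The threshold is a p "value < 0.05 will be considered statistically significant". It does not say whether these tests use visit values or change, and it names no baseline adjustment.

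The article does not spell out the scale of the change score. A difference in the recorded unit, T1 minus T0 in mV, is the natural reading.

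**The concern.** MEP amplitude is positive and may differ several-fold between patients. Table 2 admits FMA-UE scores from 20 to 50, a wide span of impairment. If stimulation raises excitability by a similar proportion in everyone, the mV change is that proportion times the starting amplitude, so it partly measures where the patient started.

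The Discussion itself asks whether benefit depends on residual corticospinal integrity. If it does, better-preserved patients have both larger mV changes and larger FMA-UE gains. The planned correlation would then be read as support for the mechanism even though relative change in excitability plays no part. This is a question of validity as well as power, and it bears on one of the trial's stated objectives.

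**Working it through.** **1. Inputs from the documents.** Amplitude is in mV, change runs from baseline to post-intervention, the test is Spearman, and the level is 0.05. The sample size section says "power analysis (power = 0.80, two-tailed α = 0.05) indicated that 45 participants would be required", which is 15 per arm, and "Accounting for an anticipated 15% dropout rate, we will recruit 18 participants per group, for a total sample size of 54". The dropout step checks: 45/0.85 = 52.9, so 53, or 54 in equal arms. The effect size behind 45 ("this translates to an effect size *f* of ~0.30") concerns upper-limb motor improvement. No mean, SD, effect or power is given for MEP, so there is no MEP figure to reproduce. Whether 45 follows from that effect size is a separate matter and is not used here.

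**2. Why the scale matters.** With a proportional gain g, raw change = baseline × (g − 1), while the log-ratio = ln g whatever the baseline. As an illustration, assume a median of 0.5 mV, a between-patient log-SD of 0.9 and g = 1.5:

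- One SD below the median: 0.5 × e^(−0.9) = 0.20 mV, raw change +0.10 mV.
- One SD above: 0.5 × e^(0.9) = 1.23 mV, raw change +0.61 mV.
- Log-ratio for both: ln 1.5 = 0.405.

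The raw changes differ about sixfold and rank differently; the log-ratios are equal. Ranking keeps the order of the raw differences, so it keeps the baseline ordering within them.

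**3. False association under Spearman, N = 45.** Assumed: lognormal amplitude, between-patient log-SD 0.6-1.2, log error 0.25 per visit, and FMA-UE gain correlated r with baseline integrity but unrelated to relative MEP change. There were 4,000 simulated trials per setting. Share with p < 0.05:

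| Uniform MEP gain | r | Raw mV change | Log-ratio |
|---|---|---|---|
| none | 0.3 or 0.5 | about 5-6% | about 5-6% |
| 30% | 0.3 | 9-14% | 5-6% |
| 30% | 0.5 | 17-29% | 5-6% |
| 50% | 0.3 | 14-21% | 5-6% |
| 50% | 0.5 | 31-50% | 5-6% |

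A separate set of runs with gains of 30-50% gave 12-35% for raw change and about 5% for the log-ratio; the grid above brackets it. The excess appears only when MEPs rise on average, which is what the trial hopes to see.

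**4. Power of the correlation, N = 45.** Assumed: true correlation 0.4, between-patient log-SD 0.5-1.1.

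- If FMA-UE change tracks proportional MEP change: raw 62-69%, log-ratio 73-75%.
- If it tracks absolute mV change: raw 73-74%, log-ratio 59-67%, a loss of 7-15 points.

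**5. Between arms, 15 per arm.**

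- Rank-sum on raw change, with a 50% gain in one arm and log-SD 0.6, 0.9, 1.2: 82%, 77%, 71%, against 84%, 83%, 84% on the log-ratio. The losses are 2, 6 and 13 points.
- Unadjusted post-treatment values, with an additive effect of +0.25 mV, within-patient log-SD 0.3 and between-patient log-SD 0.8 and 1.1: t-test 21% and 10%, rank-sum 38% and 27%. Log amplitude adjusted for log baseline gives 91% in both. Rank-sum on raw change gives 69% and 61%.

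**6. Absent MEPs.** The Discussion raises them, and a recordable MEP is not an inclusion criterion. Under the proportional model with log-SD 0.8 and 10/20/30/40% absent, Spearman power is 69/64/57/51% for the log-ratio with those patients excluded, and 59/52/45/39% for raw change with their change set to zero. With a 50 µV floor, baseline-adjusted log amplitude gave 65-95% power in the between-arm settings run, including additive effects and 20-30% absent. No test in the plan exceeded 82%, and rank-sum on raw change gave 57-63% with 30% absent.

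**The case against.** **Between-arm tests.** A reader might infer that these also use raw change scores. The text states change scores only for the mechanism correlation. If the rank-sum test is run on visit values, taking logs changes nothing, because ranks are preserved; what would help there is baseline adjustment. This stands, and the between-arm part is limited accordingly.

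**Dominance by large MEPs.** A reader might infer that patients with large MEPs dominate the results. With proportional change, the top baseline quartile carries 60-84% of the squared variation in raw change but 40-48% of the rank variation that Spearman uses. Skewed between-arm data also go to the rank-sum test, so the steep t-test losses (to 58% and 42% at log-SD 0.9 and 1.2) describe a test that the plan would normally avoid. Nor do the high correlations of 0.51-0.74 between the size of the change and baseline apply, because Spearman uses signed change. Signed raw change correlates 0.26-0.36 with error-free baseline at a 30% gain and 0.00 with no average gain. That is moderate, but it is enough for the false associations shown.

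**The log-ratio is not neutral.** Through regression to the mean it correlates −0.30 to −0.16 with observed baseline. It is undefined at zero, and the floor matters. With log-SD 0.9, 20% absent and 30% of those recovering a small MEP, a t-test on the log-ratio had 33% power with a 0.005 mV floor and 67% with 0.05 mV. At 30% absent, the rank-sum test on the log-ratio was below raw change under both floors (44% and 53%, against 54-55%). So a claim that the change costs nothing is not supported. The reversal is specific to that floor and test combination and did not occur for baseline-adjusted log amplitude with a 50 µV floor.

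**Detail for the analysis plan.** Transformation and zero handling often belong there. But the article itself names the unit, the score and the test, so it has made a choice that can be assessed.

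**Conclusion.** The point holds for the mechanism correlation. If MEPs rise on average in proportion to baseline, and FMA-UE gain depends on corticospinal integrity, the planned Spearman test can report a link that relative excitability change did not cause, in roughly 12-35% of trials against about 5% for a log-ratio. Without an average MEP gain there is no excess.

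For the arm comparison the weakness is the missing baseline adjustment. It costs little (about 2-13 points) against rank-sum on raw change and a great deal against tests on visit values; the text does not say which is meant.

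Every size rests on assumed lognormal amplitudes and assumed spreads. The documents do not show that effects are proportional, so raw mV change is not wrong in itself. It is a poor sole basis for the mechanism claim.

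**What to change.** In Statistical analysis:

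- Define MEP change for the mechanism correlation as log(T1 amplitude / T0 amplitude).
- Compare arms on log amplitude adjusted for log baseline amplitude, reported as percentage change.
- Set absent MEPs to a prespecified floor, for example the 50 µV already used in the article's definition of resting motor threshold, with a sensitivity analysis that excludes those patients.
- Keep the raw-mV results as supplementary.

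This takes a few sentences and no new data. The downsides to state are that results depend somewhat on the floor, and that the log-ratio loses about 7-15 points of correlation power if function tracks absolute mV change. The supplementary raw-mV analysis covers that second case.

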In recent years, our understanding of neuromodulatory mechanisms has continued to evolve. The “W-shaped” nonlinear model, originating from research on cognitive aging, posits that the relationship between cortical excitability and neural function is not linear (13). This model asserts that both excessively high and low states of cortical excitability are maladaptive, leading to impaired behavioral performance, while optimal cognitive function corresponds to an intermediate “optimal functional zone.” Although this model was developed in the cognitive domain, the core principle it reveals—the “excitability-function relationship” —likely represents a universal operating principle for neural networks. This is corroborated by the work of Buss et al., (14) which demonstrated that in cognitively healthy older adults, higher cognitive reserve is associated with lower motor cortex excitability. This suggests that a more optimized, moderate level of excitability forms the foundation for efficient neural processing. Critically, this principle provides a novel, integrative lens through which to understand post-stroke motor dysfunction. The classic post-stroke imbalance between hemispheres—characterized by hypoexcitability in the affected motor cortex and hyperexcitability in the unaffected hemisphere—precisely mirrors the two dysfunctional states at the extremes of the “W-shaped” model. Therefore, synergistically driving motor cortical excitability toward the central “optimal functional zone,” rather than merely applying unidirectional facilitation or inhibition, should constitute a more effective regulatory strategy. However, existing pTBS protocols have yet to leverage this theoretical framework. They typically lack a bidirectional design capable of simultaneously driving both hyper- and hypo-excitable neural circuits toward the “optimal functional zone” in an agonist-antagonist manner.

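### The mechanism analysis names a cortical silent period that is not among the listed measurements, and its only specified full-sample test can show an association but cannot confirm or refute an intermediate optimum of excitability.

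*Protocol article*

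**What the plan says.** The Abstract (Anticipated results) expects clinical gains to correlate with "neurophysiological changes (MEP amplitude, cortical silent period), supporting the central-peripheral synergy model". The Statistical analysis section takes change from baseline to post-intervention "for each participant in MEP amplitude (or cortical silent period) and in the Fugl-Meyer Assessment for Upper Extremity (FMA-UE) scores" and continues: "We will then use Spearman correlation analysis to determine whether a significant correlation exists between these two change scores". It expects larger clinical gains to go with more beneficial excitability changes, without saying which direction is beneficial. No arm term or stratification is mentioned.

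The Outcome measures section fixes the TMS recording: the stimulator "will deliver 0.2-Hz stimuli to the affected-hemisphere M1 hand area while the participant rests". It then gives a closed list that opens with "The following metrics will be obtained: (1) resting motor threshold (RMT), defined as the lowest stimulus intensity eliciting", continues with "MEP peak-to-peak amplitude (mV) measured at 120%RMT, averaged across 10 artifact-free trials" and ends with MEP latency. Table 1 has a row for MEPs and none for the silent period.

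On the model, the Introduction says that "both excessively high and low states of cortical excitability are maladaptive" and presents the trial as the first randomized test of that W-shaped model. The last paragraph of the Discussion says the trial tests whether an optimal zone exists in individuals.

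**The concern.** Three things do not fit together.

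- **Variable.** A silent period is an interruption of voluntary muscle activity, so a recording made at rest does not yield one. If it is wanted, it must be in the recording procedure before data collection ends. If it is not, it should not be an analysis variable. With two candidate predictors and no rule for choosing, a reader cannot tell which correlation was planned.
- **Shape.** Under an intermediate optimum, the same rise in excitability helps a participant who starts low and harms one who starts high. A correlation of raw change scores is monotone and ignores the starting point.
- **Arms.** The Abstract expects Group 3 to gain most clinically and expects neurophysiology to move with it. If the arms are pooled, that pattern alone can produce a correlation with no link inside any arm.

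At stake is what the mechanism analysis may conclude. The clinical comparison between arms is not affected.

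**Working it through.** The document gives no sample size, power or effect size for this correlation, so there is no figure to reproduce.

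**1. Silent period.** It is named in Anticipated results and in Statistical analysis. It is absent from the Outcome measures list and from Table 1. The substudy in the Discussion names TMS-EEG and H-reflex, not the silent period. No definition, recording condition or visit is given.

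**2. Detectable correlation.** Inputs: 45 completers (Sample size estimation), two-sided 0.05 and 80% power. Using Fisher's z with variance 1.06/(n − 3), the smallest detectable rho is tanh[(1.960 + 0.842) × √(1.06/42)] = tanh(0.445) = 0.42. Within one arm of 15 it is 0.68.

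**3. Shape.** Assume function = −e², with excitability e measured from the optimum. With baseline b and change d, functional change is y = −(b + d)² + b² = −2bd − d². For independent normal b and d, cov(d, y) = −2·var(d)·(mean b + mean d). The monotone signal is therefore positive when post-treatment excitability averages below the optimum, zero when it averages at the optimum, and negative above it.

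Simulated power, n = 45. All inputs are assumptions; the two figures are for noise of 1 and 1.5 times the signal SD. The squared terms are for baseline and post-treatment excitability, adjusted for arm.

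| Baseline mean (SD), mean shift | Spearman | Squared terms |
|---|---|---|
| 0 (1), 0 | 9% / 7% | >99% / 96% |
| −0.5 (1), +0.5 | 9% / 7% | 99% / 89% |
| −1 (1), +0.5 | 40% / 26% | 98% / 82% |
| 0 (1), +0.5 | 31% / 21% | 98% / 83% |
| −1.5 (0.5), +0.5 | 98% / 82% | 85% / 55% |

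Reruns of the first type of setting gave Spearman 5 to 8%. Reruns of the last row gave Spearman 79 to 94% and squared terms 44 to 75%. In the fourth row the association is negative.

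Under a purely linear more-is-better relation with no optimum, Spearman was significant in 97 to 100% of runs and the squared terms in 4 to 5%. A significant Spearman result therefore does not tell the two models apart.

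**4. Pooling.** Assume no within-arm link, unit SDs, and one of three equal arms ahead by s SD on both scores. The between-arm variance of each score is s² × (1/3) × (2/3) = 2s²/9, so the induced correlation is (2s²/9)/(1 + 2s²/9).

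| s | Induced correlation | Pooled Spearman p < 0.05 |
|---|---|---|
| 0.6 | 0.08/1.08 = 0.07 | about 7% |
| 0.8 | 0.142/1.142 = 0.12 | about 13% |
| 1.0 | 0.222/1.222 = 0.18 | about 21% |
| 1.2 | 0.32/1.32 = 0.24 | about 37% |

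The value 0.6 is the planning effect in Sample size estimation (d = 0.60), applied here to both measures as an assumption. Ranks centred within arm bring the rate back to about 5%.

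**The case against.** A reader might infer that the Spearman test cannot detect the W-shaped model, or would usually reject it if it were true. The documents do not support that. Statistical analysis offers the correlation as a test of association and does not say that it decides the model's fate. That statement is in the Discussion and refers to individual excitability shifts. The Discussion also plans a Bayesian hierarchical model in the first 30 participants. MEPs come only from the affected hemisphere, which the Introduction places on the hypoexcitable side, and there Spearman has good power and can beat the squared terms. A non-significant correlation also does not reject a model.

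A reader might also infer that silent-period data will not exist. The article condenses a fuller protocol, so all that can be said is that the article's own list and schedule leave it out. Pooling is likewise inferred from the absence of an arm term; an analysis plan not shown may stratify. At the protocol's own planning effect the inflation is small.

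All of this stands and limits the point. It does not remove the mismatch over the silent period, the open choice of predictor, or the fact that a monotone test carries no information on curvature. The Bayesian model covers 30 participants and its form is not given, so it does not fill that gap for the full sample.

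**Conclusion.** The point holds in limited form. The silent period is analysed but not listed as measured, and the predictor is not fixed. Both follow from the text alone. The specified full-sample test can show an association but cannot confirm or refute an intermediate optimum. Its power runs from about 5 to 9% when excitability straddles the optimum to about 80 to 98% when nearly all participants start well below it, and a positive result fits a simple linear relation equally well. These figures rest on an assumed inverted U, 45 completers and assumed spreads and noise. If the arms are pooled, the false-positive rate is about 7% at 0.6 SD, 13% at 0.8 SD and 37% at 1.2 SD, against about 5% after arm adjustment. The correction is worth making because it is cheap and changes what the mechanism analysis can claim.

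**What to change.** 1. Delete the silent period from Anticipated results and Statistical analysis. If it is kept, add it to the Outcome measures list, recorded under active contraction, and to Table 1.
2. Name MEP amplitude as the single predictor.
3. Keep Spearman as the test of association, make it partial on arm, and do not present it as a test of the W-shaped model.
4. Add a prespecified exploratory regression of FMA-UE change on baseline and post-treatment MEP amplitude with squared terms for both, adjusted for arm and baseline FMA-UE. The joint test of the squared terms is the test of an optimum.
5. Use a scale for MEP amplitude that allows zero, not a plain log. The Discussion raises absent MEPs and the eligibility criteria do not exclude them.

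The cost is analysis wording and a little more analysis. If the silent period is kept, each TMS visit takes a few minutes longer. The squared terms have modest power, about 30 to 75%, if nearly all participants start well below the optimum (individual settings tried ranged from 25% to 86%). A null result there should be reported as inconclusive.
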